## Abstract

**Background:**

Thyroid cancer is a very damaging disease. The most common treatment for this disease includes thyroidectomy and then using radioactive iodine (RAI). RAI has many side effects, including a decrease in salivary secretions, followed by dry mouth and oral and dental injuries, as well as increased inflammation and oxidative stress. Selenium can be effective in these patients by improving inflammation and oxidative stress and by modulating salivary secretions. So far, only one clinical trial has investigated the effect of selenium on thyroid cancer patients treated with radioiodine therapy (RIT) conducted on 16 patients; considering the importance of this issue, to show the potential efficacy of selenium in these patients, more high-quality trials with a larger sample size are warranted.

**Methods:**

This is a parallel double-blind randomized controlled clinical trial that includes 60 patients aged 20 to 65 years with papillary thyroid cancer (PTC) treated with RAI and will be conducted in Seyyed al-Shohada Center, an academic center for referral of patients to receive iodine, Isfahan, Iran. Thirty patients will receive 200 µg of selenium for 10 days (3 days before to 6 days after RAI treatment) and another 30 patients will receive a placebo for the same period. Sonographic findings of major salivary glands, salivary secretions, and sense of taste will be evaluated before and 6 months after 10-day supplementation.

**Discussion:**

Due to its anti-inflammatory and antioxidant effects, as well as improving salivary secretions, selenium may improve the symptoms of thyroid cancer treated with radioactive iodine. In past studies, selenium consumption has not reduced the therapeutic effects of radiation therapy, and at a dose of 300 to 500 μg/day, it has not had any significant side effects in many types of cancer under radiation therapy.

**Trial registration:**

Iranian Registry of Clinical Trials IRCT20201129049534N6. Registered on 16 September 2021.

**Supplementary Information:**

The online version contains supplementary material available at 10.1186/s13063-023-07470-2.

## Administrative information

Note: the numbers in curly brackets in this protocol refer to the SPIRIT checklist item numbers. The order of the items has been modified to group similar items (see http://www.equator-network.org/reporting-guidelines/spirit-2013-statement-defining-standard-protocol-items-for-clinical-trials/).

## Introduction

### Background and rationale {6a}

Thyroid cancer (TC) is more common than other endocrine malignancies and its incidence is increasing worldwide [1, 2]. TC includes three main tumor types with different histologic and clinical characteristics: differentiated thyroid carcinoma (DTC), anaplastic (undifferentiated or poorly differentiated) thyroid carcinoma (ATC), and medullary thyroid carcinoma (MTC). DTC is the most common type of thyroid cancer and has a better prognosis than others [3, 4].

One of the most important causes of thyroid cancer is environmental factors such as ionizing radiation, toxic chemical compounds, and halogenated pesticides. The amount of consumed iodine is also effective on the probability of contracting it, so both deficiency and excess consumption of iodine can lead to an increase in the probability of contracting thyroid cancer [5, 6]. Some modifiable individual factors, including weight, are also related to the possibility of contracting this type of cancer [7]. Inflammation is also an effective factor in causing and aggravating thyroid cancer. Generally, in thyroid cancer, there is an increase in inflammatory factors such as Nuclear factor kappa light chain enhancer of activated B lymphocytes (NF-κB) and C-Reactive Protein (CRP), which in turn causes the tumor to progress and worsen the patient’s condition [8–10].

Current treatments for thyroid cancer include thyroidectomy (complete or partial removal of the thyroid gland), tyrosine kinase inhibitors (TKI), and radioactive iodine (RAI). Among these, one of the most common methods includes thyroidectomy followed by the use of radioactive iodine [11–13]. The reason for using radioactive iodine is to drain thyroid remnants and control metastatic conditions [11, 13]. But it also has many side effects. One of the most important complications caused by radioiodine therapy (RIT) is its excessive entry into the salivary glands, which causes swelling and dysfunction of these glands, and as a result, saliva secretion decreases [14–19]. Following the decrease in saliva, dry mouth, and taste problems occur, which greatly affect the patient’s quality of life. Also, the possibility of tooth decay and gingivitis (gum inflammation) increases. If there is a long-term and chronic decrease in saliva, fibrosis of the oral mucous cells may even occur [20–24]. Another side effect of RIT is the creation of oxidative stress, which favors cancer recurrence [25]. It can also cause a disturbance in the modulation of inflammatory factors [26]. According to European guidelines, it is recommended to consume sour candy or chewing gum after RIT for hydration and to reduce the problems caused by decreased salivation [27], but many patients suffer from dry mouth and related problems even despite this practice [28].

Selenium is one of the essential minerals, the largest amount of which per gram of tissue is present in the thyroid gland and it affects thyroid health through its role in the structure of selenoproteins [29–31]. Selenoproteins play a role in the metabolism of thyroid hormones and the antioxidant system [32]. Selenium can help inhibit thyroid neoplasm, which is a potential effect through induction of apoptosis, stimulation of tumor suppressor genes, and antioxidant and anti-inflammatory function [33–37].

Recently, a clinical trial study investigated the effect of selenium on thyroid cancer patients undergoing RIT therapy, which reported that 300 μg/day of selenium from 3 days before to 6 days after RIT can help maintain salivary gland function [38]. This is the only trial study regarding the effect of selenium supplementation on patients with thyroid cancer under RIT treatment, which has a limited sample size (*n* = 16) [38], so this study will be conducted with a larger sample size to examine this issue.

### Objectives {7}

We aim to investigate the effects of selenium supplementation on sonographic findings of salivary glands in papillary thyroid cancer (PTC) patients treated with radioactive iodine. If this trial confirms our hypothesis, selenium supplementation may be used to improve the effects of existing treatments.

### Trial design {8}

A randomized, parallel, two-arm, double-blind, and placebo-controlled superiority clinical trial will be implemented.

## Methods: participants, interventions, and outcomes

### Study setting {9}

Our study will be performed at Seyyed al-Shohada Center, an academic center for the referral of patients to receive iodine, affiliated with Isfahan University of Medical Sciences, Isfahan, Iran.

### Eligibility criteria {10}

#### Inclusion criteria

Age between 20 and 65 yearsDiagnosis of PTC with pathological findings of thyroid tissue biopsy.Treated with radioactive iodine

#### Exclusion criteria

Suffering from sialadenitis (inflammation of salivary glands)Suffering from Sjogren’s syndromeSubjects with severe side effects after thyroidectomy who were not possible for RITCollagen vascular disease involving the salivary glands.Any surgery on the salivary glandsPregnancy and breastfeedingLack of patient permissionConsumption of food supplements in the last 3 months (Consumption of any herbal supplement, for example, curcumin, ginseng, etc., or/and any vitamin or mineral supplement, or/and any other food supplement, including omega-3, etc.).Suffering from special diseases such as diseases caused by congenital diseases, immune system defects, etc.Report any adverse effects after taking supplementsIf there is a significant change in any of the patient’s treatments during the period of intervention by the relevant doctor

#### Reason for eliminating the data

Consumption of less than 80% of selenium supplements by the patient.

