### Strategies to improve adherence to interventions {11c}

Selenium and placebo tablets will be delivered to the patients by the researcher ([name]) and during ten days of supplementation, the patients will be reminded to take the tablets by phone call. Also, patients will return the empty can of the supplement after ten days.

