## Assignment of interventions: allocation

### Sequence generation {16a}

After meeting the entry criteria, each patient will be randomly assigned to one of the two supplemental groups with selenium or placebo using the reliable random number generator website “https://www.sealedenvelope.com/simple-randomiser/v1/lists” and using a block size of four based on age and sex using the website https://www.sealedenvelope.com/simple-randomiser/v1/lists, with the ratio of 1:1. Sample patients will be 20 to 65 years old. Therefore, the age threshold of 20 to 65 years will be considered. For the randomization, the stratification factors are age (20 to 45, or 46 to 65) and sex (male or female).

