### Methods in analysis to handle protocol non-adherence and any statistical methods to handle missing data {20c}

The analysis will be done in an intention-to-treat format so that the data from excluded patients are also mentioned in the results. The reason for each patient’s withdrawal, especially the presence of any side effects, will be mentioned in detail. A sensitivity analysis will also be done. Missing data will be checked by multiple imputations.

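### Patients or their data are removed for events after randomisation, which contradicts the stated intention-to-treat analysis

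*Protocol article*

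**What the plan says.** Four parts of the protocol article bear on who is analysed.

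- **Eligibility criteria {10}, final subsection.** Under the heading "Reason for eliminating the data" the only entry is "Consumption of less than 80% of selenium supplements by the patient".
- **Exclusion criteria.** The last item excludes a patient after a significant change in any of their "treatments during the period of intervention by the relevant doctor". The item before it concerns reporting adverse effects once supplements have been taken.
- **Sequence generation {16a}.** "After meeting the entry criteria, each patient will be randomly assigned to one of the two supplemental groups". The ten-day capsule course follows.
- **Item {20c}.** "The analysis will be done in an intention-to-treat format so that the data from excluded patients are also mentioned in the results". It adds "A sensitivity analysis will also be done" and "Missing data will be checked by multiple imputations".

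On adherence, item {11c} gives phone reminders and says that "patients will return the empty can of the supplement after ten days". The Discussion adds that selenium biomarkers cannot be afforded.

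**The concern.** Randomisation makes the two arms comparable at the moment of allocation. A rule that later drops patients because of what happened to them, such as poor intake or a change of treatment, gives up that protection. Those dropped may differ in prognosis from those kept, and the difference need not be the same in both arms.

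An intention-to-treat analysis exists to prevent this. It keeps each randomised patient in the allocated arm whatever happens afterwards. Mentioning the data of excluded patients is a reporting commitment and does not place them in the comparison. Data cannot be both eliminated and analysed as randomised, so two analysts could follow this text faithfully and analyse different sets of patients. The primary comparison of CRP and the sonographic findings is at stake, together with a sample size that leaves almost no room for removals.

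**Working it through.** **1. When can each rule operate?**

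| Rule | Timing |
|---|---|
| Intake below 80% | After randomisation only: intake is known only once the course is under way |
| Treatment change during the intervention | After randomisation only |
| Adverse effects after taking supplements | Probably after randomisation, but could mean earlier intolerance |

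The first two are enough to create the contradiction.

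**2. What the 80% rule means.** 0.80 × 10 capsules = 8, so seven or fewer taken (three or more missed) triggers elimination.

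**3. Does the rest of {20c} resolve it?** No. The sensitivity analysis has no stated content and is not tied to the 80% rule. The imputation sentence does not say whether eliminated values are used, dropped, or set to missing and imputed.

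**4. The planned sample size reproduces.** Inputs from Sample size {14}: SD 10.9, difference 8, two-sided α 0.05, power 80%.

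n per arm = 2 × (1.96 + 0.84)² × 10.9² / 8² = 29.1, rounded up to 30, so 60 in total. No allowance for removals or losses is stated. The planned effect is 8 / 10.9 = 0.73 SD.

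**5. Power if both arms lose the same share** (assumed rates; the document gives none). Normal approximation: power = Φ(8 / (10.9 × √(2/n)) − 1.96).

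| Removed | n per arm | Power, normal | Power, t-test |
|---|---|---|---|
| 0% | 30 | 81.1% | 79.8% |
| 10% | 27 | 76.9% | 75.4% |
| 20% | 24 | 72.0% | 70.2% |

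To keep 30 analysable per arm while still removing patients would take 30 / 0.9 = 33.3, so 34 per arm at 10%, or 30 / 0.8 = 37.5, so 38 per arm at 20%.

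**6. Bias, as an illustration only.** Let a fraction f of one arm be removed, and let those removed be k SD worse than those retained. The full-arm mean equals the retained mean plus f × k, so removal shifts that arm's mean by f × k. The type I error column assumes no true effect and removal from that arm alone.

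| f | k (SD) | Shift (SD) | CRP units (× 10.9) | Share of 8 | Two-sided type I error |
|---|---|---|---|---|---|
| 0.10 | 0.5 | 0.05 | 0.55 | 7% | 5.4% |
| 0.10 | 1.0 | 0.10 | 1.09 | 14% | 6.6% |
| 0.20 | 0.5 | 0.10 | 1.09 | 14% | 6.5% |
| 0.20 | 1.0 | 0.20 | 2.18 | 27% | 11.3% |

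If both arms lose patients with the same gap k, the net shift is (f₁ − f₂) × k, which is zero when the fractions are equal.

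**The case against.** The strongest reply is that this is loose wording around a sound intention. The plan names intention-to-treat, multiple imputation and a sensitivity analysis, and if all three were carried out properly no data would be lost. That is fair as a guess at intent. It does not settle what the text instructs, because the elimination rule is stated without limitation and {20c} does not override it.

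Four stronger readings are tempting, and the document does not support them.

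- **That only the selenium arm is filtered.** The rule names selenium alone. However, items {16b} and {17b} keep the labels A and B undisclosed until the statistical analysis is complete, so a blinded team could not apply it to one arm. Reminders and can returns apply to all patients. Loose wording for the study capsule is the likelier explanation, though it still needs correcting.
- **That harms will be understated.** Items {11b}, {20c} and {22} promise reasons for withdrawal and full reporting of side effects. What remains is that a patient excluded for an adverse effect may leave the six-month comparison.
- **That the bias favours selenium by a known amount.** The removal rates and the outcome gap above are assumptions, and similar removal in both arms would largely cancel. The SD scale also fits CRP but not echogenicity, margin or contour, which are primary as well.
- **That adherence rests on the empty can alone.** Item {11c} does not say that the can is the only measure, and a can returned with capsules would show missed doses. A journal article may also leave counting details to the full protocol. The point is only that an 80% threshold needs a count.

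**Conclusion.** The point stands as a contradiction that must be resolved before the analysis. Two stated rules remove patients or data on events that can occur only after randomisation, a third may do so, and the article also claims intention-to-treat. Followed as written, the elimination rule gives a comparison that is no longer the randomised one.

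Confidence in the contradiction is high because it rests on the text alone. The size of the consequence is uncertain. The direction and size of any bias cannot be computed from the document; the 0.05–0.20 SD range depends on assumed one-arm removal of 10–20% and an assumed gap of 0.5–1 SD. The fall in power from about 81% to about 77–72% depends on assumed equal removal of 10–20% and the normal approximation. The sample-size arithmetic itself is not in dispute.

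**What to change.** Reconcile the exclusion list, the data-elimination rule and item {20c}.

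1. In {20c}, state that all randomised patients are followed to six months and analysed in their allocated arm, whatever their adherence, adverse effects or treatment changes, with multiple imputation for values that are truly missing.
2. Remove the 80% elimination rule from the primary analysis. Keep it only for a labelled secondary per-protocol analysis, worded for the study capsule, applied identically to both arms and based on a count of returned capsules.
3. Take the treatment-change item out of the eligibility list as a reason to drop data. Do the same for the adverse-effect item if it is meant to apply after randomisation; if it means earlier intolerance, say so. Whether such events stop study treatment is a separate clinical matter, on which this point takes no position.

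The cost is protocol wording and asking patients to return leftover capsules in the container they already bring back. No extra patients are needed, and the six-month visit is already planned. The downside is that the estimated effect may become slightly less favourable.

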### Informed consent procedures {26a}

In this study, after providing written and oral explanations about the objectives and method of conducting the research, written informed consent will be obtained from the patients if they wish to cooperate in the study.

### Additional consent provisions for collection and use of participant data and biological specimens {26b}

The consent form received from the patients includes their agreement to use the data in related future studies. Of course, patients can only agree to the current study and not accept future studies.

## Interventions

### Explanation for the choice of comparators {6b}

While receiving standard treatment, patients will be placed in one of two groups receiving a selenium supplement or placebo. The treatment group will receive one selenium capsule containing 200 µg of selenium per day and the control group will receive one placebo capsule containing 200 µg of maltodextrin per day for 10 days (3 days before to 6 days after radioactive iodine treatment).

The reason for choosing 200 µg is that a dosage of 200 µg/day per extra-dietary supplementation of selenium is generally considered safe and adequate for an adult of average weight [39]. In addition, the supplements available in the Iranian market have a dose of 200 μg per tablet. Also, Lee et al.’s study [38], which is somewhat similar to our study, used a dose of 300 μg. Therefore, 200 μg is close to this dose.

### Intervention description {11a}

Both treatment and placebo groups will be treated with radioactive iodine. The treatment group will receive one selenium capsule containing 200 µg of selenium per day for 10 days (3 days before to 6 days after radioactive iodine treatment). The control group will receive a placebo capsule containing 200 µg of maltodextrin per day for 10 days (3 days before to 6 days after radioactive iodine treatment). Selenium capsules are purchased from 21st Century company and the placebo is prepared by the Faculty of Pharmacy of Isfahan University of Medical Sciences. During the intervention, the type and dosage of the drugs used by the patients will not be changed, and the patients will receive all their usual treatments according to the previous routine (under the supervision of a specialist endocrinologist), and receiving selenium or placebo is merely a supplement to the common treatments they receive.

### Criteria for discontinuing or modifying allocated interventions {11b}

Each participant will be allowed to withdraw from the study at any time. Also, the reasons for each individual’s withdrawal from the study will be explained in detail in the study results.

### Strategies to improve adherence to interventions {11c}

Selenium and placebo tablets will be delivered to the patients by the researcher ([name]) and during ten days of supplementation, the patients will be reminded to take the tablets by phone call. Also, patients will return the empty can of the supplement after ten days.

### Relevant concomitant care permitted or prohibited during the trial {11d}

The patient will receive all the usual care and treatment under the supervision of a specialist doctor. There will be no change in receiving standard care during the study. Patients only received selenium supplements or a placebo in addition to receiving routine treatments.

### Provisions for post-trial care {30}

All standard treatments will be continued after the study, but selenium or placebo supplements will only be received for 10 days during the study.

### Outcomes {12}

In general, the variables evaluated in this study will include demographic variables, assessment of disease severity, and evaluation of changes in sonographic findings of major salivary glands (including echogenicity, size, margin, and contour in sonography).

Demographic variables (including age, gender, marital status, smoking, medical history and medical history, education level, occupation, and use of supplements and drugs) will be collected from all participants by completing a general information questionnaire.

Before and 6 months after the 10-day intervention with selenium or placebo, sonography was taken from parotid and submandibular salivary glands and according to sonography, these salivary glands will be evaluated in terms of echogenicity, size, margin, and contour.

Huang et al.’s study including 446 patients with thyroid carcinoma, reported that the side effect of radioactive iodine on salivary glands occurs after a few months [40]. Also, Lee et al.’s study, which investigated the effect of selenium intake on reducing the side effects of radioactive iodine on salivary glands, examined the findings after 6 months [38]. Therefore, we will examine the changes in salivary gland sonographic findings after 6 months.

The level of taste sensation and secretion of salivary glands will be evaluated by the evaluation questionnaire of the level of sialadenitis [41]. This questionnaire contains 14 questions and each question can have between 1 and 4 scores (score 1, not at all; score 2, a few times; score 3, fairly often; and score 4, almost always.). Therefore, the overall score varies between 14 and 56 [41].

Before and 6 months after the 10-day intervention with selenium or placebo, 10 ml of blood will be taken from the patients and collected in plastic tubes. A centrifuge will be used to separate the serum samples. Then the serum will be poured into 0.5 ml microtubes. The samples will be stored in a freezer at − 70 °C. To reduce the error in the measurements, all blood samples will be taken at 8–10 am in the fasting state.

CRP will be evaluated at the beginning and end of the study, and if there will be no budget restrictions, we will also evaluate total antioxidant capacity (TAC) and superoxide dismutase (SOD).

### Participant timeline {13}

The study flow diagram is according to Table 1 and Figs. 1 and 2.

